	**Ratings**: sweetness and fattiness identity and intensity (score) **SDT parameters**: d′ (sensory sensitiviy), C and ß (response bias based on cognitive strategy)	11-point anchored Likert-type scale (scores from 0 to 10) designed to measure taste perception	Sussex Ingestion Pattern Monitor (SIPM™ 2.0); Sussex University; UK	Primary	Study 1
	**Ratings**: pleasantness of the taste (score)/thirst and hunger level (score)/familiarity of food samples.	Time-intensity measures for pleasure; opportunity to scale the perceived liking dynamically over 60 sec. Labeled magnitude scale for thirst/hunger	SensoMaker™; UFLA, Brazil	Primary/secondary	Study 1 & 2
Behavioural	**Facial expressions**: general emotions, valence and actions units (intensity score)	Positive/negative valence as measure of overall affection; general emotions (joy, anger, surprise, fear, contempt, sadness, disgust); action units as the likelihood of specific facial muscle activations	FACET™ SDK; iMotions Inc., Cambridge Innovation Center, US	Primary	Study 1 & 2
Psycho-physiological	**Cardiovascular**: heart rate and heart rate variability	Cardiovascular Changes as index of cardiac sympathetic activation and autonomic arousal	Module—GSR & Heart Rate and ECG/EMG; Shimmer3 EMG/ECG, GSR Kit and EXG Devices; iMotions Inc., Cambridge Innovation Center, US	Primary	Study 2
	**Electrodermal activity**: skin conductance level (μmhos), skin conductance response rate (count/min)	Changes in the conductivity of skin as index of sympathetic activation		Primary	Study 2
	**Facial electromyography**: EMG powers (mV)	EMG activity of the levator labii (disgust), corrugator supercilia (general negative affect) and zygomatic major (pleasure) muscle regions		Primary	Study 2

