R-AN	Training session to habituate to the testing environment	A vs. B, A vs. C, A vs. D, B vs. C, B vs. D, C vs. D	A vs. B, A vs. C, A vs. D, B vs. C, B vs. D, C vs. D
C-AN			
U-CT			
N-CT			
R-BN			
C-BN			

*A, B, C, D, samples of ice cream with a high-/low-sweet and high-/low-fat taste. The order of the paired samples and conditions (swallow and spit) will be randomized. R-AN, recovered anorectic; C-AN, currently ill anorectic; U-CT, underweight control; N-CT, normal weight control; R-BN, recovered bulimic; C-BN, currently ill bulimic. R-AN and R-BN will be assessed at discharge*.

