Carbohydrate (g)	21.8	21.8	22.1	22.1
Protein (g)	4.7	4.8	4.8	4.8
Fat (g)	1.2	1.2	11.9	11.9
Kcal total	117.0	117.3	215.1	215.4
Kcal (%)	54.3	54.4	99.9	Reference = 100
Relative sweetness	14.45	28.01	14.76	28.8

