**INGREDIENTS (%)**				
Whole milk	0.0	0.0	35.0	35.0
Skimmed milk	45.6	45.6	0.0	0.0
Cream	0.0	0.0	27.2	27.2
Water	27.1	27.1	11.0	11.0
Skimmed milk powder	7.6	7.6	4.2	4.2
Sucrose	8.7	8.7	6.8	6.8
Dextrose	4.3	4.3	4.5	4.5
Glucose DE 35–40%	2.2	2.2	1.5	1.5
Sweetener (Aspartam)	0.0	0.1	0.0	0.1
Stabilisator/emulfiser	0.8	0.8	0.7	0.7
Chocolate powder	0.9	0.9	0.8	0.8
Cocoa powder	2.8	2.8	2.6	2.6
Color (E150d)	0.6	0.6	2.0	2.0
Flavor	0.1	0.1	0.1	0.1
Polydextrose	0.0	0.0	4.5	4.5
Whey powder	0.0	0.0	2.0	2.0

*The high fatness and high sweetness is the food sample reference for kcal*.

**Table 6 T6:** Preliminary sensory testing results (*N* = 5; normal weight individuals) for the food samples with low and high content of fatness and sweetness.

**Attribute**	**Food sample**			
	**Low fatness and low sweetness**	**Low fatness and high sweetness**	**High fatness and low sweetness**	**High fatness and high sweetness**
Sweetness	2.75	5.96	3.50	6.25
Creaminess	2.17	3.42	4.96	5.50
Chocolate flavor	4.08	4.58	4.17	4.63
Caloric content	3.00	5.83	5.21	6.50

*The attributes were rated in a scale from 1 (not sweet, not creamy, too week, very low) to 7 (very sweet, vey creamy, too intensive, very hing)*.

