#### Planned analysis

Analyses will be adjusted for covariates, namely the scores of EDE-Q, BDI-II, FCQ-T-Reduced, TSF-T-Reduced, and hunger and thirst levels. Additional covariates can be added to the model if necessary. In study 1, the procedure for computing the variance of d′, confidence intervals for d', chi-square tests of significance for d′ and comparisons of multiples d′s among groups across two testing conditions will be performed for sweetness, creaminess and caloric content scores according to the Bi et al. (1997) and Bi (2008) approach. Analogous to d′, confidence intervals, hypothesis tests and multiple comparisons for C and ß will be constructed according to Kadlec's (1999) approach.

In study 2, differences in T–I parameters (Imax, Tmax, AUC), self-ratings (hedonic, familiarity) and intensity of facial expressions (emotion, valence and actions units), as well as the cardiovascular, electrodermal and facial electromyographic outcomes, will be analyzed using mixed, three-way factorial ANOVAs with group (six levels) as between-subjects and testing condition (swallowing vs. sip-and-spit) and food sample (four levels) as within-subjects' factors. Additionally, a time series emotional analysis for assessing emotional responses to beverages will be applied to automated facial expression data using the Wilcoxon signed-rank test (Crist et al., 2016) if more sensitive analysis are needed to detect differences between groups. Outcome variables will be checked for normal distribution. Note that linear mixed models to analyse the data can be envisaged to have more statistical power to detect actually existing study effects and to lead to less biased results in the case that the intraclass correlation coefficient and the design effect show dependency in the data (Hox, 1998). Statistical analyses will be conducted using SPSS (IBM, SPSS; Version 23.0, Chicago, IL, USA). Descriptive statistics will be presented using Mean ± *SD* for all continuous variables.

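### Study 1 plans d′, C and ß for caloric content, but two of the six pairs are practically isocaloric and the other four can be answered from belief, so calorie d′ cannot separate sensitivity from cognition as H1 requires

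*Protocol article*

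**What the plan says.** The Planned analysis section commits to variances, confidence intervals, chi-square tests and group comparisons of d′ across both testing conditions. These "will be performed for sweetness, creaminess and caloric content scores". The same section gives C and ß analogous tests.

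Data processing presents d′ as a sensitivity measure that bias does not affect. It explains d′ = 0 as inability to tell levels of sweetness or fatness apart; caloric content is not mentioned there. The expected results section adds caloric content to the weight-related attributes and takes a similar high d′ as evidence of good discrimination in all groups.

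Table 3 presents every pair of the four samples in each condition: "A vs. B, A vs. C, A vs. D, B vs. C, B vs. D, C vs. D". Table 5 gives their energy, in the order low-fat/low-sweet, low-fat/high-sweet, high-fat/low-sweet, high-fat/high-sweet: "Kcal total 117.0 117.3 215.1 215.4". The sweetness contrast comes from one ingredient: "Sweetener (Aspartam) 0.0 0.1 0.0 0.1". Table 6 gives pilot ratings in the same order: "Caloric content 3.00 5.83 5.21 6.50".

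The Table 2 row that carries d′, C and ß as primary for Study 1 describes its ratings as "sweetness and fattiness identity and intensity (score". Caloric content is not in it.

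**The concern.** A d′ needs a correct answer on each trial, because hits and false alarms are counted against it. For sweetness and fat the recipe supplies that answer. For calories it does so only where fat differs, since the sweetener adds almost no energy.

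H1 holds that patients have intact sensory performance and that weight-related cognition appears in response bias. The belief that sweet food is high in calories is such a cognition. If that belief moves d′, a difference in belief between groups, or between swallowing and spitting, can appear as a sensory difference or hide one. C and ß use the same hit and false-alarm rates, so they inherit the problem.

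**Working it through.** **Inputs.** Energy, relative sweetness and ingredients from Table 5; pilot ratings from Table 6; pairs from Table 3; the d′ formula from Data processing. Table 3 does not map the letters to samples, but all six pairs are used, so the counts hold under any mapping.

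**Reproducing Table 5.** Energy relative to the reference is 117.0/215.4 = 54.3%, 117.3/215.4 = 54.5% (printed as 54.4, a rounding difference) and 215.1/215.4 = 99.9%. A 4/4/9 kcal per gram check gives 116.8, 117.2 and, for both high-fat samples, 214.7 kcal. The energy figures are sound.

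**All six pairs** (second sample minus first; LF/HF = low/high fat, LS/HS = low/high sweetness):

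| Pair | kcal | Relative sweetness | Pilot caloric rating | Judged by fat | Judged by sweetness |
|---|---|---|---|---|---|
| LF/LS, LF/HS | +0.3 | +13.56 | +2.83 | no real answer | no real answer |
| HF/LS, HF/HS | +0.3 | +14.04 | +1.29 | no real answer | no real answer |
| LF/LS, HF/LS | +98.1 | +0.31 | +2.21 | right | near chance |
| LF/LS, HF/HS | +98.4 | +14.35 | +3.50 | right | right |
| LF/HS, HF/LS | +97.8 | −13.25 | −0.62 | right | wrong |
| LF/HS, HF/HS | +98.1 | +0.79 | +0.67 | right | near chance |

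In the first two rows the energy difference is 0.3/117.0 = 0.26% and 0.3/215.1 = 0.14%.

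**Two perfect tasters, scored on the four pairs that differ in energy.** With no position bias F = 1 − H, so d′ = [z(H) − z(F)]/√2 = √2·z(proportion correct).

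- Judging calories by sweetness alone: (1 + 0 + 0.5 + 0.5)/4 = 0.50, so d′ = √2·z(0.50) = 0. The Excel expression without √2 also gives 0.
- Judging by fat: 4/4 correct, so d′ is at its maximum.
- Sensitivity check: if the first taster could always resolve the small sweetness differences in the two near-chance pairs, she would score 3/4, and d′ = √2 × 0.674 = 0.95, still far below the second.

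Sensory ability is the same in both; only the rule linking taste to calories differs.

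**Scoring by expected calories instead.** This gives the two isocaloric pairs an answer, but a hit then means agreement with the belief, and d′ measures how firmly it is held.

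**Pilot.** In both isocaloric pairs the sweeter sample is rated more caloric (3.00 v 5.83; 5.21 v 6.50). The low-fat/high-sweet v high-fat/low-sweet pair is rated against its true order (5.83 v 5.21). Table 6 gives no SD. If the rating noise is assumed to be 1 to 2 points, with Pc = Φ(difference/(SD·√2)), the sweeter sample would be chosen in 98% to 84% of trials on the low-fat isocaloric pair and in 82% to 68% on the high-fat one. These percentages are illustrations only.

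**The case against.** Several points on the other side stand.

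- **Outcome status.** A reader might infer that calorie d′ is a primary outcome. The document does not establish this: the primary row in Table 2 names only sweetness and fattiness, and caloric content enters later, in the planned analysis and the expected results. What is documented is a mismatch between those sections.
- **Sweetness and creaminess.** A reader might also infer that d′ for these attributes is diluted and capped, because two pairs are nearly equal in relative sweetness and two are equal in fat. That assumes all six pairs are pooled. Table 3 says which pairs are presented, not which enter each d′, and an article may leave that to the full protocol. It also assumes chance performance on those pairs, whereas the pilot rates them differently: sweetness 2.75 v 3.50 and 5.96 v 6.25, creaminess 2.17 v 3.42 and 4.96 v 5.50.
- **The reversed pair.** It is a gap of 0.62 on a 1-to-7 scale from five "normal weight individuals" without an SD. It is a warning sign and not an established effect.
- **Direction of bias.** If patients held the belief more strongly, their calorie d′ would fall, which works against the predicted similarity. The plan cannot be said to favour its own hypothesis here.
- **Design intent.** The samples were deliberately selected to differ in expected calories. That supports keeping the calorie question, but not treating its d′ as belief-free sensitivity.

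None of this supplies a correct answer for the isocaloric pairs or removes belief from the other four.

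**Conclusion.** The concern holds for caloric content. Two of six pairs have no usable calorie signal. On the remaining four, tasters of identical ability can range from d′ of about 0 to the maximum, depending on the cue they use. This rests on Table 5 and on the stated plan to test d′ for caloric content; it needs neither the pilot data nor any assumed SD. The value of 0 assumes near-chance choice on the two pairs of nearly equal sweetness; the extreme alternative is 0.95. Calorie d′ therefore cannot carry the planned reading as good sensory discrimination. C and ß for caloric content share the defect because they come from the same rates. How large the distortion would be in the actual groups cannot be derived from the document.

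**What to change.** Limit the signal-detection measures used to test H1 (d′, C and ß) to sweetness and fattiness/creaminess, in line with Table 2 and Data processing. Remove caloric content from the signal-detection analysis in the planned analysis and expected results sections. Report it as an expectancy outcome, for example the proportion of choices in which the sweeter of two isocaloric samples is judged more caloric, by group and by swallow/spit condition. The isocaloric pairs suit this well, because sensory access to real energy cannot explain the choice.

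As a secondary clarification, state that d′ for sweetness and for fattiness uses the pairs designed to differ in that attribute (four of six in each case).

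The cost is a change of analysis wording, with no new samples, participants or sessions. One of three planned signal-detection attributes is replaced, and four rather than up to six pairs per condition enter each d′, so individual estimates are less precise.

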H1: If perceptual disturbances in AN and BN are related to biased cognitions about gaining weight rather than to gustatory deficits or BMI, then AN and BN patients should respond with similar sensory performance but higher response bias scores in a discrimination test, (1) compared to non-ED underweight, normal-weight and illness-recovered controls, and (2) during a swallowing compared with a sip-and-spit condition.H2: If fear of weight-gain in restricting-type AN elicits taste aversion, then facial electromyographical, facial expression, and autonomic and subjective correlates of disgust (Kappas, 2003; Kreibig, 2010) while tasting high-sweet and high-fat foods should be observed compared to (1) stimuli of low-sweet and low-fat foods; (2) non-ED underweight, normal-weight, illness-recovered controls and (3) BN patients; and (4) especially during the swallowing compared with the sip-and-spit condition.H3: If avoidance of energy-rich foods in BN reflects a cognitive preoccupation about the increased liking of very sweet tastes associated with gaining weight, then facial electromyographical, facial expression, and autonomic and subjective correlates of pleasure (Kappas, 2003; Kreibig, 2010) while tasting high-sweet foods should be observed compared to (1) fat and low-sweet stimuli; (2) non-ED underweight, normal-weight, illness-recovered controls and (3) restrictive-type AN; and (4) no differences between swallowing and sip-and-spit conditions.

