### Statistical and analytic plan

#### Sample size calculation

Sample size calculations were based on findings of small to medium effects on eating behavior in patients with anorexia and bulimia by our group (e.g., Munsch, 2014) using the software G^*^Power (version 3.13). Assuming two-sided tests with Alpha = 0.05, Beta = 0.2, and effect size *f* = 0.20, the required sample size would be 80 to ensure a power >0.80 in each one of the two studies with a sample distribution of N_C−AN_ = 15, N_C−BN_ = 15, N_R−AN_ = 10, N_R−BN_ = 10, N_U−CT_ = 15, and N_N−CT_ = 15. To obtain the required number of 50 patients per study and taking into account a participation rate of 80% and a dropout rate of 20% in the patient population, a total of 60 patients per study will be needed. Based on our recruitment and testing experiences in Switzerland and Luxembourg (average annual recruitment of 35–40 AN and 35–40 BN patients), the access to a sufficiently powered sample of patients seems to be guaranteed. Finally, in order to achieve the sample size suggested by the power analysis, a sample of 30 healthy controls (university students) per study will be recruited in Fribourg.

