### The expected results

Concerning the study 1, the main results to be expected are that a different and reduced C (*C* < 0) and (ß < 1) are expected in currently-ill AN and BN patients compared to non-ED underweight, normal-weight and illness-recovered controls, and during a swallowing compared with a sip-and-spit condition. Reduced C and ß-values would show a response bias to say, “Yes, the gaining weight-related attribute [sweetness, creaminess and caloric content] is present.” By contrast, patients will have a similar high d′ value compared with control groups, which means that all the participants have a good sensory discrimination.

Concerning the study 2, it is mainly predicted that restricting-type AN will show evidence of reduced verbal ratings as well as bodily higher corrugator activity, disgust facial expressions and heart rate acceleration in response to high-sweet and high-fat foods compared to stimuli of low-sweet and low-fat foods; non-ED underweight, normal-weight, illness-recovered controls and BN patients; and especially during the swallowing compared with the sip-and-spit condition. On the other hand, higher zygomatic muscle activity and more smiles expressions in response to very sweet tastes will be expected to observe in BN compared to fat and low-sweet stimuli; non-ED underweight, normal-weight, illness-recovered controls and restrictive-type AN; and no differences between swallowing and sip-and-spit conditions.

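### Study 2 tests two directed hypotheses with a six-group omnibus ANOVA; on shared outcomes a bulimia effect alone can reject it, and pooled contrasts fit H2 and H3 better

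*Protocol article*

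**What the plan says.** The Hypothesis text below Figure 1 sets out two separate, directed predictions for Study 2.

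- H2 opens "If fear of weight-gain in restricting-type AN elicits taste aversion". It expects signs of disgust at high-sweet and high-fat food in restricting-type anorexia, compared with low-sweet and low-fat samples, with the control and recovered groups, and with bulimia, and more so when the food is swallowed (clause 4).
- H3 expects signs of pleasure at high-sweet food in bulimia, against its own named samples and groups, with no difference between swallowing and spitting (clause 4). The section on expected results repeats this: "higher zygomatic muscle activity and more smiles expressions in response to very sweet tastes will be expected to observe in BN".

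The Planned analysis section gives Study 2 one main model, fitted to each outcome: "mixed, three-way factorial ANOVAs with group (six levels) as between-subjects" factor, with testing condition (two levels) and food sample (four levels) within subjects. A linear mixed model is mentioned as an option, and a Wilcoxon time-series analysis if more sensitivity is needed. Neither is tied to H2 or H3. Multiple comparisons are named for Study 1 only.

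The sample size section sets f at 0.20, beta at 0.2 and a two-sided alpha of 0.05. Its conclusion is that "the required sample size would be 80 to ensure a power >0.80 in each one of the two studies". Within each study, the planned group sizes are "N_C−AN_ = 15, N_C−BN_ = 15, N_R−AN_ = 10, N_R−BN_ = 10, N_U−CT_ = 15, and N_N−CT_ = 15".

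**The concern.** With six groups and four samples, the group × food test has 5 × 3 = 15 numerator degrees of freedom. Its null is that all six food profiles are parallel. H2 concerns one group on one sample, and H3 concerns another group on two samples. The omnibus test responds to a departure by any group in any direction, so rejection does not say which hypothesis the data favour. It also spreads a one-group prediction over 15 degrees of freedom.

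Two things are at stake. On an outcome that both hypotheses use, a significant interaction could be reported as support for taste aversion in anorexia when bulimia produced it. Conversely, a real effect in one disorder could be missed although the same data would show it in a focused comparison.

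**Working it through.** **The plan's own figure.** The stated 80 per study at f = 0.20 cannot be reproduced without further inputs. The article does not say which effect f refers to, how many repeated measures were entered, or their correlation. With six groups and correlation 0.5, a repeated-measures interaction needs 86 women for two measurements, 64 for four and 45 for eight; a one-way group test needs 327. Four measurements give 80 if the correlation is about 0.36. This does not show that 80 is wrong, but it cannot be tied to H2 or H3.

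**Inputs.** From the article: group sizes 15/15/10/10/15/15, N = 80, two-sided alpha 0.05, two conditions, four samples. Assumed: outcome SD 1, equal within-person correlation 0.5, no covariates, and the four samples are the four ice creams. H2 is taken as a shift of size d in C-AN on the sample high in both sweetness and fat. H3 is taken as a shift of d in C-BN on both high-sweet samples.

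**Omnibus group × food test.** Averaged over the two conditions, the error variance of a normalised food contrast is (1 − 0.5)/2 = 0.25. If one group of 15 departs, the noncentrality is

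λ = 15 × (1 − 15/80) × S / 0.25 = 48.75 × S,

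where S is the sum of squared deviations of that group's profile from its own mean. For the H3 pattern (0, d, 0, d), S = d². For the H2 pattern (0, 0, 0, −d), S = 0.75 d². Power comes from the noncentral F with 15 and 222 degrees of freedom.

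| Who departs | d | λ | Omnibus rejects |
|---|---|---|---|
| C-BN only | 0.4 | 7.80 | 0.33 |
| C-BN only | 0.5 | 12.19 | 0.53 |
| C-BN only | 0.6 | 17.55 | 0.73 |
| C-AN only | 0.5 | 9.14 | 0.39 |

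A 4,000-run simulation of the full design agrees: with C-BN alone shifted by 0.3, 0.42 and 0.6 SD, the test rejected in 19%, 36% and 73% of runs. In the same runs a contrast of C-AN against R-AN and the two control groups stayed at 5%, and so did the group × food × condition test.

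**Pooled contrasts, 74 degrees of freedom.** The target group is compared with the mean of both control groups and its own recovered group. The group part of the variance is 1/15 + (1/9)(1/15 + 1/15 + 1/10) = 0.0926.

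- H2: the sample high in both minus the mean of the other three has variance 0.25 × (1 + 1/3) = 1/3. SE = √(0.0926/3) = 0.176, and 0.5/SE = 2.85. Power is 0.80, or 0.56 at 0.05/6.
- H3: the mean of the high-sweet minus the mean of the low-sweet samples has variance 0.25. SE = √(0.0926 × 0.25) = 0.152, and 0.5/SE = 3.29. Power is 0.90, or 0.72 at 0.05/6.

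**Why pool.** C-AN against N-CT alone has SE = √((1/3) × 2/15) = 0.211 and noncentrality 2.37. Power is 0.65 unadjusted, and 0.28 at the first Holm step if the comparisons are split into 13 pairs. That is below the omnibus 0.39.

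**Both disorders depart.** With C-AN shifted by 0.48 SD and C-BN by 0.42 SD, the simulated omnibus test rejects in 79% of runs. The pooled C-AN contrast rejects in 76%.

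**The case against.** The strongest reply is that a factorial ANOVA is a reasonable model, that the hypotheses already name their comparisons, and that a condensed article may leave follow-up contrasts to a fuller document that is not shown. This stands in part. The absence of a contrast list is not the finding. The finding is that the test the article does name does not match the hypotheses it states.

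Several stronger readings are tempting, and the article does not support them.

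- *Any bulimia effect makes the anorexia test significant.* It can, at the rates above, but need not. There is one ANOVA per outcome, and the outcomes are partly separate: corrugator activity and disgust expressions for anorexia, zygomatic activity and smiles for bulimia. A rise in zygomatic activity in bulimia cannot make the corrugator ANOVA significant.
- *Every part of H2 is contaminated.* The three-way term behind clause 4 is not triggered by the bulimia pattern that H3 predicts. Clause 3 compares anorexia with bulimia, so a bulimia effect belongs there.
- *Power is halved throughout.* The loss depends on the effect pattern and on how strictly the contrasts are adjusted, and it largely disappears if both effects exist, as the study predicts.
- *The two-mechanism claim will be read from significance in one group and not in the other.* The article states no such rule, and its model contains group × condition terms. What remains is that H3 clause 4 predicts no difference, and a non-significant result in 15 women would not establish that.

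**Conclusion.** The concern holds in a limited form. On shared outcomes, a significant group × food interaction does not by itself support H2, because a bulimia effect of 0.4 to 0.6 SD alone produces one about 33% to 73% of the time. If only one disorder departs, by 0.5 SD, focused pooled contrasts are clearly more powerful, and they keep an advantage at the strictest Holm step of six.

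The sizes rest on the assumed correlation of 0.5, the assumed effect shapes and an analysis without covariates, none of which the article supplies. The mismatch between the omnibus null and the two hypotheses does not depend on those assumptions. This does not undermine the design, but it is worth correcting before the data are analysed.

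**What to change.** Name a short list of one-degree-of-freedom contrasts from the fitted model as the tests of H2 and H3, apply Holm across the list, and describe the omnibus F tests as descriptive.

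1. H2: C-AN against the mean of U-CT, N-CT and R-AN, on the high-sweet/high-fat ice cream minus the other ice creams.
2. H2: C-AN against C-BN, on the same food contrast.
3. H2, clause 4: contrast 1 applied to swallow minus spit.
4. H3: C-BN against the mean of U-CT, N-CT and R-BN, on high-sweet minus low-sweet.
5. H3: C-BN against C-AN, on the same food contrast.
6. Two mechanisms: the C-AN minus C-BN difference in swallow minus spit, with its confidence interval, in place of reading a non-significant bulimia result as no difference.

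Keep the comparators pooled; splitting them into pairs gives the gain away. The cost is analysis-plan wording and a few contrast statements on the same data. The small downside is that the contrasts must be fixed in advance and unpredicted group patterns become exploratory.
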